### Randomization

Older individuals who meet the inclusion criteria following the baseline assessment and sign the informed consent will be randomized into one of two VR protocols: conventional or multimodal. Randomization will be accomplished by a statistical computer program, by blocks. The block randomization will be gradually performed during the study according to the number of eligible participants registered on the waiting list. Hence, the block sizes will not be fixed and will vary from 4 to 12 subjects, concerning the minimum and maximum capacity for VR at the Otoneurology outpatient clinic. Blocks will therefore eventually be composed of an odd number of participants, and as a consequence unequal groups could be formed. Block randomization was preferred in order to prevent time-related influences from disturbing the homogeneity of both groups over the data collection period (2 years and 6 months). Sample randomization and allocation will be performed by a researcher who is not involved in the clinical trial. In order to assure concealed allocation, the treating therapist will be informed by telephone call regarding the allocation of each participant just before their first session.

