### Sample size calculation

The estimated sample size was calculated considering previous DHI and DGI (primary outcomes) results based on a previously published trial
[25], which compared VR outcomes in young versus older adults with vestibular disorders. The *t* test was used to detect clinical difference between means of continuous variants (primary outcomes) with 80% power, and 5% significance level. Estimations indicated that 34 individuals were required for the DGI (effect size = 2.5; standard deviation = 3.5) and 32 individuals for the DHI assessments (effect size = 14; standard deviation = 20), where effect size is the mean difference expected between the two groups and standard deviation is for the population. Hence, a minimum of 68 patients will be necessary for the sample. To minimize the effects of the dropout rate, at least 15% more individuals will be required to compose the final sample.

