### Statistical analysis

The effects of the VR protocols will be tested through both intention-to-treat and per-protocol analysis. For the intention-to-treat analysis, missing post-treatment or follow-up outcomes data will be replicated from previous measures available (assuming no change for noncompleters). For per-protocol analysis, data from excluded subjects will be disregarded for analysis. The groups will be compared at baseline by the chi-square test for qualitative data and by the *t* test for quantitative data. To analyze changes in outcomes at baseline, post-treatment, and follow-up between and within groups, analysis of variance with repeated measures will be applied. A normality test will be applied to the outcome measures; when data are not normally distributed, equivalent nonparametric tests will be used. Potential interactions between treatment and covariates, such as age, sex, comorbidities, medications, dizziness features, psychocognitive aspects, adherences and follow-up data, will also be tested. The results will be presented as frequencies/percentages for categorical variables, and as means, medians, standard deviations and 95% confidence intervals for continuous variables. Data analyses will be performed using SPSS for Windows version 17.0 (SPSS Inc., Chicago, IL, USA) and the significance value for all tests will be set at *P* <0.05.

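### The only analysis named for change in DHI and DGI treats the pre-randomisation baseline as a response level, with no baseline adjustment and no named between-arm contrast

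*Protocol article*

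**What the plan says.** The Statistical analysis section gives one method for change in the outcomes: "To analyze changes in outcomes at baseline, post-treatment, and follow-up between and within groups, analysis of variance with repeated measures will be applied". It does not call this the primary analysis, but it names no other for the two primary outcomes, the Dizziness Handicap Inventory (DHI) and the Dynamic Gait Index (DGI).

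Baseline scores enter in one other way, through tests between the arms: "The groups will be compared at baseline by the chi-square test for qualitative data and by the *t* test for quantitative data". Covariates appear only as possible effect modifiers: "Potential interactions between treatment and covariates, such as age, sex, comorbidities, medications, dizziness features, psychocognitive aspects, adherences and follow-up data, will also be tested". The outcome's own baseline score is not in that list. Results are to be given "as means, medians, standard deviations and 95% confidence intervals for continuous variables", and no between-arm difference is mentioned.

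Two other sections bear on the point. Outcome measures places the baseline assessment before randomisation, with retests at 8 weeks and 3 months. Sample size calculation rests on a simple two-group comparison: "The *t* test was used to detect clinical difference between means of continuous variants (primary outcomes) with 80% power, and 5% significance level".

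**The concern.** A score taken before randomisation cannot carry a treatment effect. Using it as a response level has two consequences.

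- The group main effect averages a true difference with a zero.
- The treatment question moves into the group-by-time interaction. With three visits this is an omnibus 2-df test, and by itself it gives no difference at 8 weeks or at follow-up.

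Using the same score as a covariate removes between-person variation from the comparison. At stake is power in a trial planned for 80% with 34 per arm. Also at stake is whether the report will state how far apart the two protocols are on DHI and DGI, with an interval. Because within-group analysis is planned alongside, a reader could also end up comparing two within-arm P values, which is not a comparison of the protocols.

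**Working it through.** **Inputs from Sample size calculation.** DHI: difference 14, SD 20, so d = 14/20 = 0.70. DGI: difference 2.5, SD 3.5, so d = 2.5/3.5 = 0.714. Power 80%, significance level 5% (two-sided assumed), total 68, hence n = 34 per arm.

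**Assumptions not in the article.** Equal arms, equal SD at each visit, and the same correlation r between any two visits, taken as 0.3, 0.5 and 0.7.

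**Step 1: the plan's own figure.** The exact two-sample t test needs 32 per arm for DGI and 34 for DHI. The larger gives 2 × 34 = 68, as stated. (The article attaches 34 to DGI and 32 to DHI; the total is unaffected.) At 34 per arm, power for DHI is 81.2%.

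**Step 2: noncentrality for DHI, same effect at both post-baseline visits.** The differences by visit are (0, 0.70, 0.70), their mean is 0.4667, and n/2 = 17.

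- Group main effect, 1 and 66 df: λ = 17 × 0.4667² / [(1 + 2r)/3]. The 14-point difference is read as 14 × 2/3 = 9.33.
- Group-by-time, 2 and 132 df: λ = 17 × [0.4667² + 2 × 0.2333²] / (1 − r) = 5.553/(1 − r).
- 8-week ANCOVA, 1 and 65 df: λ = 17 × 0.70² / (1 − r²) = 8.33/(1 − r²).
- ANCOVA on the mean of the two post-baseline scores, 1 and 65 df: λ = 8.33 / [(1 + r)/2 − r²].

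**Step 3: results.**

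| Analysis (DHI, sustained effect) | r = 0.3: λ, power | r = 0.5: λ, power | r = 0.7: λ, power |
|---|---|---|---|
| Group main effect | 6.94, 74% | 5.55, 64% | 4.63, 56% |
| Group-by-time | 7.93, 70% | 11.11, 85% | 18.51, 98% |
| 8-week ANCOVA | 9.15, 85% | 11.11, 91% | 16.33, 98% |
| ANCOVA, mean post-baseline | 14.87, 97% | 16.66, 98% | 23.14, 99.7% |

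At r = 0.5 the group-by-time test and 8-week ANCOVA have the same λ. The 6-point gap there is the price of spending two degrees of freedom.

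**Step 4: the named contrast.** The single contrast from baseline to 8 weeks has λ = 8.33/[2(1 − r)] = 5.95, 8.33 and 13.88, giving 67%, 81% and 96%. It estimates the right quantity, but less precisely than ANCOVA, since 2(1 − r) exceeds 1 − r² whenever r < 1.

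**Step 5: effect halved by follow-up.** Group-by-time power falls to 57%, 73% and 92%. The 8-week ANCOVA is unchanged at 85%, 91% and 98%. These are tests of different questions, so this comparison supports naming a time point more than it measures a loss of efficiency.

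DGI follows the same pattern. With a sustained effect, group-by-time has 72%, 86% and 98%, and 8-week ANCOVA 86%, 92% and 98%.

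**The case against.** The strongest reply is that the planned model is valid and contains the answer. The section speaks of changes between groups, and the group-by-time contrast is an unbiased between-arm difference in change in a randomised trial. That stands. A reader might infer that the plan cannot give the between-arm difference; the article does not support that. What it lacks is a statement of which contrast, at which visit, will be reported. If that were the only gap, a condensed article could leave it to a fuller document. The remaining fault is in the method that is stated.

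The power loss also depends on an unknown correlation. With a sustained effect, group-by-time reaches 80% from r of about 0.44, and by r = 0.7 it matches 8-week ANCOVA (97.5% against 97.8%). So a flat claim that power is wasted would go too far.

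Other stronger readings that do not hold:

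- Nothing says the diluted group main effect will be the treatment test. Its figures show only what would follow if it were read that way.
- Nothing says within-arm P values will be used to rank the protocols. With equal benefit and 80% power in each arm, one arm alone would be significant in 2 × 0.8 × 0.2 = 32% of trials, but that 80% is an assumption. If both arms improved by 18 DHI points, the article's threshold for significant improvement, within-arm power would be about 99.0% at r = 0.3 and 99.9% at r = 0.5. Discordance would then be only about 2% and 0.2%.
- Sizing on a t test and analysing with a repeated-measures model is common practice and not a contradiction.
- The Randomization section explains the blocks: "Block randomization was preferred in order to prevent time-related influences from disturbing the homogeneity of both groups". Leaving them out of the model is minor. Any gain rests on an intraclass correlation that the article does not give, and the omission errs on the conservative side.

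**Conclusion.** The point holds as a matter of efficiency and of an unnamed estimate; it is not one of validity. For a sustained DHI effect, moving from the omnibus group-by-time test to 8-week ANCOVA gains about 14 points of power at r = 0.3, 6 at r = 0.5 and almost nothing at r = 0.7. Against ANCOVA on the mean post-baseline score the gains are about 26, 13 and 2 points. If the group main effect were read as the treatment test, power would be below the planned 80% throughout that range. These figures assume 34 per arm, equal correlation and variance at all visits, and the article's own difference and SD. The correlation itself is assumed. The change should be made because it uses data already collected and yields a defined treatment estimate.

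**What to change.** Before outcomes are compared by arm, replace the repeated-measures ANOVA for DHI and DGI with a linear mixed model on the 8-week and follow-up scores. Include arm, visit, arm-by-visit, the baseline score as covariate, and a random participant effect. Enrolment block may be added as a minor refinement if it was kept with the allocation record.

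Report the adjusted between-arm difference with its 95% CI at each visit, with 8 weeks named as the main time point. Present within-arm changes as descriptive only, and say that they are not evidence that one protocol is better.

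The cost is analysis wording. Table 1 shows both scores collected at all three visits. The Trial status section puts the end of the study in September 2012 with outcome analysis still to come, so the change should be dated and described as made after data collection but before comparison by arm.

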## Discussion

The VR protocols are considered effective at reducing dizziness and its consequences
[14,18]. However, there are few randomized clinical trials that investigate VR effects on exclusively older subjects, who, in addition to the vestibular disorder, present other impairments related to ageing that may negatively influence body balance control. Consideration of these conditions in addition to vestibular exercises might offer improve outcomes in this population. Since the Cawthorne&Cooksey VR protocol has already been recognized as effective, we believe that its modification with the inclusion of other components of postural control could improve its performance for older individuals with chronic dizziness. Both protocols are simple, require minimal resources and can be executed in various therapeutic settings, which enables their widespread use in case beneficial outcomes be observed. The comparison between rehabilitation protocols designed for older people with vestibular disorders would enable better planning and managing of interventions to diminish dizziness symptoms, functional disability and body imbalance, and to prevent falls in this population.

## Trial status

The study was concluded by September 2012. Outcome analysis and publish data will be performed on 2013.

## Abbreviations

DGI: Dynamic Gait Index; DHI: Dizziness Handicap Inventory; TUG: Time Up and Go Test; UNIFESP: Federal University of São Paulo; VR: vestibular rehabilitation.
